**Amended 17 April 2008**

## **5.16. Collection of covariates**

Data for the calculation of covariates will be collected during this study (refer to Section 10.9.5). Study center, bednet use, geographical area, distance from health center and altitude of subject's permanent residence above sea level will be determined from the existing demographic surveillance systems in place at each site.

For bednets, a field worker will visit the home of the subject during the study (refer to Section 5.13 for timepoints) and make a direct observation of whether the child's bed has a bed net and if so, whether or not it is intact. He will ask the family whether the bednet is impregnated.

For indoor residual spraying, the field worker will ask whether the child's bedroom has been sprayed by a residual spraying program. Refer to Section 5.13 for timepoints of the fieldworker's visit.

*Amended 23 October 2006*

## **6. INVESTIGATIONAL PRODUCTS AND ADMINISTRATION**

### **6.1. Study vaccines**

The candidate vaccines to be used have been developed and manufactured by GSK Biologicals.

The Quality Control Standards and Requirements for the candidate vaccine are described in separate release protocols and the required approvals have been obtained.

Commercial vaccines are assumed to comply with the specifications given in the manufacturer's Summary of Product Characteristics.

Refer to Appendix G for details of vaccine supplies.

#### **6.1.1. RTS,S/AS01E vaccine**

The RTS,S/AS01E vaccine consists of two fractions: the lyophilized fraction containing the RTS,S antigen in one vial and the liquid fraction, consisting of AS01E adjuvant in the other vial, to be used for reconstitution just prior to injection. A dose of 0.5 mL will be injected. The presentation of the reconstituted RTS,S/AS01E candidate malaria vaccine is an opalescent liquid.

##### **6.1.1.1. RTS,S antigen presentation:**

- The RTS,S antigen is presented as a lyophilized pellet in a 3 mL monodose vial. One dose contains approximately 25 µg of antigen with sucrose as cryoprotectant.

**6.1.1.2. AS01E adjuvant:**

- AS01E is presented in a 3 mL monodose vial. One dose contains 25 µg of MPL and 25 µg of Stimulon® QS21 (a triterpene glycoside purified from the bark of *Quillaja saponaria*) with liposomes.

**6.1.2. Sanofi-Pasteur's Human Diploid Cell Rabies Vaccine**

Sanofi-Pasteur's Human Diploid Cell Rabies Vaccine is a sterile freeze-dried suspension of rabies virus prepared from strain PM 1503-3M obtained from the Wistar Institute, Philadelphia, PA.

The potency of one dose (1.0 mL) of Sanofi-Pasteur's Human Diploid Cell Rabies Vaccine is at least 2.5 IU of rabies antigen. Sanofi-Pasteur's Human Diploid Cell Rabies Vaccine is a creamy white to orange, freeze-dried vaccine for reconstitution with the diluent prior to use; the reconstituted vaccine is a clear to slightly opaque, colorless suspension.

A dose of 1.0 mL will be injected. The presentation of the reconstituted vaccine is as a pink to red liquid. One dose of Sanofi-Pasteur's Human Diploid Cell Rabies Vaccine contains less than 100 mg albumin, less than 150 µg neomycin sulphate and 20 µg phenol red indicator. The vaccine contains no preservative or stabilizer.

Amended 20 December 2006

**6.2. Dosage and administration**

The vaccinees will be observed closely for at least 60 minutes following the administration of vaccines, with appropriate medical treatment readily available in case of an anaphylactic reaction.

**6.2.1. RTS,S/AS01E**

RTS,S/AS01E will be supplied such that the reconstituted vaccine volume will provide a 0.5 mL pediatric dose. One 0.5 mL dose will be withdrawn from each vial and used.

Disinfect top of vaccine vial (pellet) and adjuvant vial with alcohol swabs and let dry. Withdraw the contents of the adjuvant vial in a syringe and inject adjuvant into the vial of lyophilized antigen. Remove and discard the syringe and needle under appropriate safety precautions. The pellet is then dissolved by gently shaking the vial. Wait for 1 minute to ensure complete dissolution of vial contents before withdrawing a sufficient volume to provide a 0.5 mL dose (volume required for RTS,S/AS01E) of the reconstituted vaccine solution using a fresh needle and syringe for injection. The reconstituted vaccine should be administered by slow intramuscular (IM) injection, using a 25G needle with length of 1 inch (25 mm), in the left deltoid muscle within 4 hours of reconstitution (storage at +2°C to +8°C).

**6.2.2. Sanofi-Pasteur's Human Diploid Cell Rabies Vaccine**

Disinfect top of vaccine vial with alcohol swabs and let dry. Inject the entire contents of the diluent *syringe* into the vaccine vial. Keeping the syringe and needle in place, the freeze-dried vaccine is dissolved by gently shaking the vial. Wait for 1 minute to ensure complete dissolution of vial contents before withdrawing a sufficient volume to provide a 1.0 mL dose still using the original needle and original syringe. The original needle should then be replaced with a fresh needle for IM injection. The reconstituted vaccine should be used immediately.

Amended 20 December 2006

**6.3. Storage**

**ALL VACCINE VIALS/PRE-FILLED SYRINGES AND ADJUVANTS MUST BE STORED IN THE REFRIGERATOR (+2°C to +8°C) AND MUST NOT BE FROZEN.**

All vaccines will be stored in a safe and locked place with no access for unauthorized personnel. Storage temperature will be monitored daily, according to SOPs at the investigator's site. An alarm system and a back-up refrigerator will be available in case of power failure/breakdown.

The study monitor must be contacted if the cold chain is broken (e.g. vaccines become frozen or refrigeration fails).

Storage conditions for transport of vaccines from country medical department or dispatch center to study sites or between sites are described in Appendix D.

**6.4. Treatment allocation and randomization****6.4.1. Randomization of supplies**

There will be a separate randomization list supplied to each site with no overlap of Treatment Numbers. The randomization list will be generated at GSK Biologicals, Rixensart, using a standard SAS (Statistical Analysis System) program and will be used to number the vaccines.

In this randomization process, volunteers will be allocated randomly to one of two study groups defining which vaccine should be given (i.e. RTS,S/AS01E or Rabies vaccine). Each group will have the same number of subjects.

**6.4.2. Randomization of subjects**

Subjects will receive Study ID cards with Subject Numbers at the screening visit (Clinic Visit 1). Subject numbers will be issued consecutively at each site; there will be no overlap of subject numbers allocated at each site. At first vaccination visit (Clinic Visit 2 [Month 0]), after verification of eligibility criteria, subjects will be allocated a Treatment

Number in the order they present for vaccination with the lowest Treatment Number available from the randomization list for their site. The correspondence between the Subject Number and the Treatment Number will be noted down in the Clinic Form and subsequently transferred to the Case Report Form.

In order to minimize the potential for imbalance in malaria transmission exposure between recipients of RTS,S/AS01E and recipients of control vaccine, potential study subjects will be invited according to their area of residence to attend on specified days for vaccination. They will be randomized in the order that they present.

**The actual treatment number used for first vaccination of the subject must be recorded by the investigator in the CRF (Rando/Treatment Allocation Section).**

## **6.5. Method of blinding and breaking the study blind**

Data pertaining to RTS,S/AS01E or rabies vaccine will be collected in a double blinded (observer blinded) manner. 'Double blinded (observer blinded)' means that the vaccine recipient and their parent(s)/guardian(s) as well as those responsible for the evaluation of safety and immunogenicity endpoints will all be unaware which treatment, RTS,S/AS01E or rabies vaccine, was administered to a particular subject. The only study staff aware of the vaccine assignment for RTS,S/AS01E or rabies vaccine will be those responsible for the storage and preparation of vaccines; these staff will play no other role in the study.

Code break envelopes, for each study enrolled subject and associating each treatment number with a specific vaccine, will be kept by the Local Safety Monitors in Kenya and Tanzania as well as by Central Safety at GSK Biologicals, Rixensart in a safe and locked place with no access for unauthorized personnel.

If deemed necessary for reasons such as safety or to guide treatment in a subject exposed to rabies, the relevant Local Safety Monitor together with the GSK Biologicals Central Safety Contact will unblind the specific enrolled subject.

A formal reporting and analysis plan (RAP) will be developed. Once the study is completed and the GSK Biologicals reference database locked, GSK Biologicals will be responsible for initiating the execution of the statistical analysis plan in collaboration with KEMRI, JMP and MVI and breaking the blind.

GSK Biologicals' policy (incorporating ICH E2A guidance, EU Clinical Trial Directive and Federal Regulations) is to unblind any serious adverse event (SAE) report associated with the use of the investigational product, which is unexpected and attributable/suspected, prior to regulatory reporting. The Clinical Safety Physician is responsible for unblinding the treatment assignment in accordance with specified time frames for expedited reporting of SAEs (Refer to Section 8.8).

## **6.6. Replacement of unusable vaccine doses**

Additional vaccine doses will be provided to replace those that are unusable (see Appendix G for details of supplies).

In addition to the vaccine doses provided for the planned number of enrolled subjects, 3% additional doses will be supplied. In case a vaccine dose is broken or unusable, the investigator should replace it with a replacement vaccine dose. If a vaccine dose needs replacement, the envelope with the corresponding treatment number will designate the replacement without unblinding the study using a coded letter system. Although the sponsor need not be notified immediately in these cases, documentation of the use of the replacement vaccine must be recorded by the investigator on the vaccine administration page of the CRF and on the vaccine accountability form.

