Vaccines will be administered in an observer-blinded fashion. For each vaccination during the course of the study, the Vaccine Preparer will prepare the vaccine and the Vaccinator administer the vaccine for a specific subject. Since the vaccines used in this study are of distinct appearance, the Vaccine Preparers are not blinded and together with the Vaccinators perform no other function in the study (refer to Section 6.5). The Vaccine Preparer will select the sealed box labeled with the appropriate treatment number, (containing the vials numbered with the treatment number), remove the vaccine vials and fill a syringe according to this study protocol (refer to Section 6.2). The Vaccine Preparer will then place a numbered opaque label with the subject's treatment number on the syringe. The purpose of masking the syringe is to blind the parent(s) or guardians(s) of the subject. The Vaccine Preparer will then pass the syringe to the Vaccinator in an adjacent room who will administer the vaccination. After administering the vaccine to the subject, the Vaccinator will enter the treatment number administered to the subject on the clinic form.

Subjects who cannot be vaccinated on the originally scheduled date (see Section 4.6.1) will be vaccinated within 7 days and undergo all study procedures for the visit on the same day as vaccination. In the particular case of any child found to be febrile (axillary temperature  $\geq 37.5^{\circ}\text{C}$ ), a blood slide will be taken to investigate for malaria. Children will be treated as appropriate for their condition and will be followed up until resolution of any symptoms and be vaccinated if their clinical symptoms resolve within 7 days.

Those who cannot be re-vaccinated within 7 days of their scheduled date will continue all study procedures apart from receiving further study vaccinations.

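### Protocol 6.6 makes the investigator, who judges AE causality, replace defective doses, a task 5.3 and 6.5 reserve for unblinded staff; followed literally, it can unblind an AE assessor

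*Protocol*

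**What the plan says.** Four parts of the Protocol bear on this.

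- **Section 6.6 (replacement of doses).** "In case a vaccine dose is broken or unusable, the investigator should replace it with a replacement vaccine dose". An envelope matched to the treatment number "will designate the replacement without unblinding the study using a coded letter system". Afterwards, "documentation of the use of the replacement vaccine must be recorded by the investigator on the vaccine administration page of the CRF", and also on the vaccine accountability form.
- **Section 5.3 (vaccination process).** "Since the vaccines used in this study are of distinct appearance, the Vaccine Preparers are not blinded"; they "together with the Vaccinators perform no other function in the study". The handling itself is theirs: "The Vaccine Preparer will select the sealed box labeled with the appropriate treatment number", and they then take out the vials and fill the syringe. The outer boxes of the two vaccines are identical.
- **Section 6.5 (blinding).** The only study staff who know the assignment "will be those responsible for the storage and preparation of vaccines; these staff will play no other role in the study". Those who evaluate safety and immunogenicity endpoints are to be unaware of it.
- **Section 8.5.2 (causality).** The investigator must judge the relationship of each AE and SAE to the investigational product. Solicited injection-site reactions are counted as related without that judgement.

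**The concern.** The blind in this trial depends on separating people, because the products cannot be made to look alike. Whoever handles the vials knows the arm, so 5.3 and 6.5 confine that knowledge to staff who do nothing else. Section 6.6 hands one piece of vial handling to a person on the other side of the barrier.

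At stake is the blinded assessment of adverse events in the double-blind phase. Apart from solicited local reactions, causality is a matter of the investigator's clinical judgement. An assessor who has seen which product a child received can be influenced by it. A replacement also occurs at a vaccination, which is when the 7-day solicited and 30-day unsolicited follow-up windows open.

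**Working it through.** No stated figure in the plan is in dispute, so the check is mainly a comparison of the passages.

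**Step 1. Who may handle vials.** In 5.3 the Vaccine Preparer selects the box, removes the vials and fills the syringe. In 6.5 only storage and preparation staff may know the assignment. In 6.6 the person who replaces a dose is the investigator. As worded, these assign overlapping work to different roles.

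**Step 2. Whether that role must be blind.** Section 6.5 requires evaluators of safety endpoints to be unaware of treatment, and 8.5.2 makes the investigator such an evaluator. The same named role therefore holds both a supply task and an evaluation task.

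**Step 3. Whether seeing the contents reveals the arm.** It does.

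| | RTS,S/AS01E (6.1.1, 6.2.1) | Rabies vaccine (6.1.2, 6.2.2) |
|---|---|---|
| Components | antigen vial and adjuvant vial | freeze-dried vial and diluent syringe |
| Reconstituted | opalescent | pink to red |
| Dose | 0.5 mL | 1.0 mL |

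**Step 4. What the safeguards cover.** The envelope tells the user which replacement to take without naming the vaccine. Identical outer boxes hide the contents while they stay sealed. Neither hides a vial once a box is open, and breakage of a vial would normally be found at that point. Section 6.6 does not say who inspects the dose, and it does not confine the investigator to opening the envelope or passing on a sealed box.

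**Step 5. Scale of the supply.** Inputs: 890 children to be enrolled, 445 per arm (Synopsis); three doses each; 3% additional doses (6.6).

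- Planned doses: 890 × 3 = 2,670.
- Spares: 2,670 × 0.03 = 80.1, about 80.
- Per arm: 445 × 3 × 0.03 = 1,335 × 0.03 = 40.05, about 40.

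This is the size of a reserve. Appendix G describes it as a minimum and lists bad storage and administration to the wrong child among its uses, so it is neither a cap on replacements nor a forecast of them.

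**The case against.** The strongest reply is that 6.6 should be read together with 5.3 and 6.5. Those are the specific rules on who touches vials, and the Protocol elsewhere uses the word investigator for site responsibility. For example, 6.4.2 has the investigator record the treatment number in the CRF, although in 5.3 the Vaccinator first writes it on the clinic form. On that reading the Preparer finds the defect and makes the replacement, and the investigator answers for it. Section 6.6 also states that the coded letters avoid unblinding, and under Appendix G the box label may carry several lot numbers when the study is double-blind.

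Much of this stands. An investigator who only opens the envelope and hands over a sealed box learns nothing about the arm. But the reader has to supply that reading, because 6.6 names the investigator and contains no limit of this kind.

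Four stronger inferences are tempting, and the documents do not support them:

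- **That following 6.6 necessarily unblinds.** It can be followed without seeing a vial.
- **That the malaria endpoint is compromised.** A case under 10.5 needs a measured temperature and a parasite density, slides are read in duplicate (Appendix F), and 5.9 and 5.10 do not have the investigator judging cases personally.
- **That about 80 of 890 children (9%) would be affected.** This requires every spare to be used, each in a different child, with the investigator viewing each one. The Protocol gives no basis for any of these.
- **That the CRF entry itself reveals the arm.** Section 6.6 asks only for documentation that a replacement was used, and the treatment number is already on the CRF in blinded form. The letter scheme is not described, so whether the letters could be linked to an arm cannot be judged.

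**Conclusion.** The role conflict is real and appears on the face of the Protocol. A site that follows 6.6 literally can breach 6.5, and a site that keeps to 6.5 may have to depart from the wording of 6.6. The consequence is a possible loss of blinding for an AE assessor, confined to children with a replaced dose and, for causality, to events other than solicited local reactions.

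The expected effect is small and cannot be quantified from the document. It depends on how often doses are replaced and on whether the investigator personally sees an open box, and neither is given. The roughly 80 spare doses describe supply only. Because the correction costs almost nothing and protects the blinded assessment of AEs, it is worth making.

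**What to change.** In section 6.6, name the unblinded Vaccine Preparer as the person who inspects the dose, decides that it is unusable, opens the coded envelope, takes the replacement and completes the accountability form. The investigator, or other blinded staff, should record on the CRF only that a replacement was used.

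The identity of the replacement should stay in the unblinded accountability record and be linked to the study data when the blind is broken after database lock (6.5). The Total Vaccinated Cohort, which 10.7.1 analyses by the treatment actually given, can then use it. It should not be added to the CRF at the Clinic Visit 6 unblinding, because that would mean editing the CRF after the lock.

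The cost is a few words in 6.6 and one form moved to staff who already handle the vials. No extra staff, data or participants are needed.

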### **6.7. Packaging**

See Appendix G.

### **6.8. Vaccine accountability**

See Appendix G.

### **6.9. Concomitant medication/treatment**

At each study visit/contact, the investigator should question the enrolled subject about any medication(s) taken.

All antipyretic, analgesic and systemic antibiotic drugs administered at ANY time during the period starting with administration of each dose and ending 30 days after each dose are to be recorded with generic name of the medication (trade names are allowed for combination drugs, i.e., multi-component drugs), medical indication, total daily dose, route of administration, start and end dates of treatment.

Amended 20 November 2006

All antimalarial drugs throughout the study period, beginning with Dose 1 are to be recorded with generic name of the medication (trade names are allowed for combination drugs, i.e., multi-component drugs), medical indication, total daily dose, route of administration, start and end dates of treatment.

Any treatments and/or medications which are listed as elimination criteria in Section 4.5, e.g., any immunoglobulins, other blood products and any immune modifying drugs administered within three months preceding the first dose or at any time during the study period are to be recorded with generic name of the medication (trade names are allowed for combination drugs only), medical indication, total daily dose, route of administration, start and end dates of treatment. Refer to Sections 4.4 and 4.5.

Any vaccine administered during the study period is to be recorded with trade name, route of administration and date(s) of administration. Refer to Sections 4.4 and 4.5.

Any Vitamin A administered from 2 months prior to Dose 1 to 30 days post Dose 3.  
Amended 23 October 2006.

Any concomitant medication administered prophylactically in anticipation of reaction to the vaccination must be recorded in the CRF with generic name of the medication (trade names are allowed for combination drugs only), total daily dose, route of administration, start and end dates of treatment and coded as 'Prophylactic'. The time periods between which each type of concomitant medication/treatment should be recorded is summarized in Table 7.

**Table 7            Summary of time periods between which different classes of concomitant medication/treatment/vaccination must be recorded**

|                                                            |                                                                                                                                                              |
|------------------------------------------------------------|--------------------------------------------------------------------------------------------------------------------------------------------------------------|
| 2 months prior to Dose 1 → Dose 1                   | All treatments listed as elimination criteria in Section 4.6*, all antimalarials, Vitamin A                                                                  |
| Dose 1 → 30 Days post Dose 3                        | All antipyretic, analgesic, systemic antibiotic, antimalarial and any treatments listed as elimination criteria in Section 4.6*, all vaccinations, Vitamin A |
| 31 Days post Dose 3 → Clinic Visit 7                | All treatments listed as elimination criteria in Section 4.6*, all antimalarials, all vaccinations                                                           |
| Clinic Visit 8 → Final study Visit (Clinic Visit 9) | All treatments listed as elimination criteria in Section 4.6*, all antimalarials, all vaccinations                                             |

\* e.g. any immunoglobulins, other blood products and any immune modifying drugs

Amended 23 October 2006

Amended 20 November 2006

